## Abstract

**Background:**

Gestational diabetes mellitus (GDM) is an increasing problem world-wide. Lifestyle interventions and/or vitamin D supplementation might help prevent GDM in some women.

**Methods/design:**

Pregnant women at risk of GDM (BMI≥29 (kg/m^2^)) from 9 European countries will be invited to participate and consent obtained before 19+6 weeks of gestation. After giving informed consent, women without GDM will be included (based on IADPSG criteria: fasting glucose<5.1mmol; 1 hour glucose <10.0 mmol; 2 hour glucose <8.5 mmol) and randomized to one of the 8 intervention arms using a 2×(2×2) factorial design: (1) healthy eating (HE), 2) physical activity (PA), 3) HE+PA, 4) control, 5) HE+PA+vitamin D, 6) HE+PA+placebo, 7) vitamin D alone, 8) placebo alone), pre-stratified for each site. In total, 880 women will be included with 110 women allocated to each arm. Between entry and 35 weeks of gestation, women allocated to a lifestyle intervention will receive 5 face-to-face, and 4 telephone coaching sessions, based on the principles of motivational interviewing. The lifestyle intervention includes a discussion about the risks of GDM, a weight gain target <5kg and either 7 healthy eating ‘messages’ and/or 5 physical activity ‘messages’ depending on randomization. Fidelity is monitored by the use of a personal digital assistance (PDA) system. Participants randomized to the vitamin D intervention receive either 1600 IU vitamin D or placebo for daily intake until delivery. Data is collected at baseline measurement, at 24–28 weeks, 35–37 weeks of gestation and after delivery. Primary outcome measures are gestational weight gain, fasting glucose and insulin sensitivity, with a range of obstetric secondary outcome measures including birth weight.

**Discussion:**

DALI is a unique Europe-wide randomised controlled trial, which will gain insight into preventive measures against the development of GDM in overweight and obese women.

**Trial registration:**

ISRCTN70595832

## Background

Europe is facing an unprecedented threat from Type 2 diabetes (T2D) with associated human suffering and an economic burden of enormous and rapidly growing proportions
[1]. While T2D is traditionally associated with a sedentary lifestyle and an unhealthy diet, the currently observed growth in developed countries is greater than expected from lifestyle deficiencies alone. Evidence is accumulating that Gestational Diabetes Mellitus (GDM) may be a more important contributor to these epidemics than previously recognised
[2,3]. Firstly, women with past GDM comprise up to 31% of parous women with T2D
[4]. Secondly, intrauterine exposure to hyperglycaemia through GDM, predisposes the off-spring to diabetes and obesity: so called “fuel mediated teratogenesis”
[5]. If GDM is acting as the “accumulator” contributing to the T2D epidemic, strategies to arrest this inter-generational transmission are urgently needed.

GDM is defined as ‘carbohydrate intolerance resulting in hyperglycaemia of variable severity with onset or first recognition during pregnancy’
[6]. GDM is characterised by pancreatic beta cell function that is insufficient to meet the body’s insulin needs, usually in association with the increasing insulin resistance of pregnancy. There is no common unique pathogenic complication of diabetic pregnancy and a continuous relationship exists between maternal glycaemia and perinatal outcomes
[7].

Like T2D in general, the prevalence of GDM in Europe is reported to vary considerably, in some populations GDM occurs already in up to 20% of all pregnancies. However, there is no generally accepted and uniform European agreement on screening approaches and diagnostic standards, making pan-European surveys of GDM currently very difficult
[8].

The pathophysiological processes associated with GDM, particularly those relating to insulin secretory capacity and underlying insulin resistance are also contributors to the development of T2D. Strategies for preventing T2D could therefore also be useful for GDM prevention. Currently no strong evidence exists regarding the best intervention for prevention of GDM
[9,10], although a low glycaemic index diet, healthy diet according to recommendations for the general population, or an exercise program could be beneficial. In addition lifestyle studies conducted specifically with overweight or obese pregnant women, potentially involving weight gain restriction, may reduce the prevalence of GDM and restrict gestational weight gain, although the quality of the published studies thus far is mainly poor
[11]. Well designed randomised trials, with standardised behavioural interventions are needed
[12].

Beyond lifestyle interventions, Vitamin D supplementation (serum 25-hydroxyvitamin D (25OHD)) has also been proposed as an approach that could prevent T2D
[13]. In pregnancy, insulin sensitivity is reduced. Normally, improved beta cell function and proliferation meet the increased secretory demands in pregnancy, but when this fails, GDM will occur. In pregnant women, an inverse correlation was found between vitamin D and insulin resistance, measured using Homeostasis Assessment (HOMA), suggesting that deficiency may contribute to insulin resistance
[14]. In women with GDM, administration of vitamin D led to a decrease in fasting glucose levels
[15]. Therefore, vitamin D is postulated to contribute to insulin sensitivity and beta cell function, and deficiency may contribute to impaired glucose tolerance (IGT) during pregnancy. Suggested mechanisms are varied and in addition to those mediated through calcium and parathyroid hormone, include effects on cytokine release and innate and adaptive immunity
[16].

This study will focus on prevention of GDM in the antenatal period and is designed to collate evidence about the epidemiology of GDM in Europe, to promote pan-European standards and measures for GDM and to identify suitable preventive measures against GDM.

## Methods/design

### Overall study design

This is a multicentre, randomized controlled trial using a 2×(2×2) factorial design across nine European countries. Pregnant women attending a participating antenatal clinic or hospital in one of these countries will be approached and asked to take part in the study. Baseline assessment will occur before 20 weeks gestation, immediately followed by randomization into one of the eight, pre-stratified intervention groups. Follow up measurements will occur at 24–28 weeks, 35–37 weeks and birth. This trial is funded by the European Union 7th framework (FP7/ 2007–2013) under Grant Agreement no. 242187, further local funding is received in some of the individual centres. All study procedures have been pilot tested and modified as necessary for the main study. The study was approved by the relevant ethical committees before the start of DALI (NRES Committee East of England – Norfolk: 11/EE/0221; Medical University Poznan: 1165/12; UZ KU Leuven: ML7625; VUmc Amsterdam: 2012/400; Hospital De La Santa Creu i Sant Pau Barcelona 13/006 (OBS); Medical University Vienna: 2022/2012 – 1369/2013; Region Hovedstaden Copenhagen: H-4-2013-005; Province of Padua: 4201 × 11; Galway University Hospitals: 7/12).

### Participants

Pregnant women with a pre-pregnancy body mass index (BMI) ≥ 29 kg/m^2^ are eligible for inclusion
[17]. Where pre-pregnancy weight is not known the most earliest antenatal weight will be used. Further inclusion criteria are: before 19+6days of gestation, singleton pregnancy and aged ≥ 18 years.

Women will be excluded from the study if they: are diagnosed with GDM on oral glucose tolerance testing, before randomization, using IADPSG criteria defined as fasting venous plasma glucose ≥ 5.1 mmol/l and/or 1 hour glucose ≥10 mmol/l and/or 2 hour glucose ≥ 8.5 mmol/l at baseline measurement
[18]; have pre-existing diabetes; are not able to walk at least 100 meter safely; require complex diets; have chronic medical conditions (e.g. valvular heart disease); have significant psychiatric disease; are unable to speak major language of the country of recruitment fluently or are unable to converse with the lifestyle coach in another language for which translated materials exist. For the vitamin D arm, two additional exclusion criteria apply: have current or past abnormal calcium metabolism, e.g. hypo/hyperparathyroidism, nephrolithiasis, hypercalciuria; have hypercalciuria (>0.6 mmol/mmol creatinine in spot morning urine) or hypercalcaemia (>10.6 mg/dl | 2.65 mmol/l) detected at baseline measurement.

Women who have developed GDM at baseline are informed that they can not participate any further in DALI and are recommended to contact their health care provider regarding their GDM. These women are asked to consent to have the information regarding their pregnancy outcomes collected. As the IADPSG criteria are not used to diagnose GDM at all sites, each site has a protocol on how to link women with appropriate services in their locality.

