#### Sample size and power calculation

The primary outcomes of the study are gestational weight gain, fasting glucose and insulin sensitivity in late pregnancy. The numbers needed in each arm (80% power, 5% significance, two tailed alpha) were calculated assuming a 20% drop out. To detect a weight gain difference of 4 kg (mean of 11 kg and standard deviation (SD) of 6.5 kg) we would need 80 women in each arm. To measure a fasting glucose difference of 0.3 mmol/l (mean of 5.0 mmol/l and a SD of 0.5 mmol/l) we would need 85 women in each arm. To find a difference 0.44 for the HOMA-IR (mean of 2.2 and a SD of 0.8) we would need 101 women in each arm. Lesser numbers are required when using the factorial design, combining cells for comparisons. The trial will be conducted in nine European countries (ten study centres) and in each centre 88 women will be recruited (total n = 880) before 20 weeks of pregnancy and randomly assigned to one of the eight arms pre-stratified for centre and 2x2 trial (lifestyle 2x2 or vitamin D/placebo 2x2).

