### Randomisation

Women who are eligible will be randomly allocated to one of the eight intervention arms (as is shown in Figure 
1): 1) healthy eating (HE), 2) physical activity (PA), 3) HE+PA, 4) HE+PA+vitamin D, 5) HE+PA+placebo, 6) vitamin D alone, 7) placebo alone, 8) control. A computerized random number generator draws up an allocation schedule pre-stratified for intervention centre and 2x2 trial. The DALI trial coordinator will prepare sealed opaque envelopes containing the intervention arm to which each participant is allocated. The outcome of the allocation will be reported by the lifestyle coach to the participant, before the start of the intervention. Those involved with measurements are kept blinded of the intervention.

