**Evaluation**						
Dose, reach, fidelity, satisfaction	Questionnaire			x		
Costs^f^, distance, visits	Questionnaire	x	x	x		

^a^ Data collected from routine and expert scans that occur during the time points.

^b^ Blood samples will be collected in the fasting state and at [30, 60, 90 and 120 minutes] or [60, and 120 minutes] depending on site following ingestion of the glucose drink (75 g D-glucose in 250 ml water).

^c^ If GDM is diagnosed by IADPSG criteria, subsequent visits only test the fasting measurements.

^d^ obtained locally only for the vitamin D arm.

^e^ at delivery only registration of adverse events.

^f^ data registration for a longer period post natal.

^g^ collection of samples in a non fasting state.

*PPAQ* pregnancy physical activity questionnaire, *PA* physical activity, *HE* healthy eating, *WHO* world health organisation.

At birth maternal blood is collected shortly before the birth process (or a day after delivery, to minimize disrupting blood levels caused by the delivery itself). Placenta tissue and cord blood is collected and processed within 30 minutes after birth. Neonatal measurements will be performed within 48 hours after birth. The women will be asked to complete a questionnaire and data from the medical records will be requested regarding the delivery.

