### Data analysis

Multilevel analyses will be performed, to take the clustering effect into account, since the success of treatment can be dependent on the skills of the provider as well as specific characteristics of a treatment centre. Longitudinal, linear regression analyses will be performed to assess intervention effects. In these analyses, the correlation between multiple measurements within one individual is taken into account. The regression coefficient reflects the average difference in the outcome variable between conditions. Possible confounders will be entered into the regression analyses. Confounding will be defined as a change in the regression coefficient of 10% or more. Possible effect modification will be studied as well, defined as a significant (p <0.10) interaction-term between group allocation and the variable concerned. Data will be analysed according to the intention-to-treat principle.

Interactions between interventions will be assessed, and when not present, groups will be combined.

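### Groups may be combined across two 2x2 trials that appear to be separate allocation strata, with no term for trial, so some pooled contrasts could carry bias

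*Protocol article*

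**What the plan says.** **Allocation.** The sample size section has women "randomly assigned to one of the eight arms pre-stratified for centre and 2x2 trial (lifestyle 2x2 or vitamin D/placebo 2x2"). The randomisation section repeats this: the number generator "draws up an allocation schedule pre-stratified for intervention centre and 2x2 trial".

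**Eligibility.** The participants section states: "For the vitamin D arm, two additional exclusion criteria apply". They are a history of abnormal calcium metabolism, and raised urinary or serum calcium at the baseline measurement. Table 1 marks the calcium tests at baseline and at both later visits, and footnote d says they are "obtained locally only for the vitamin D arm".

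**Competing wording.** The randomisation section also says "Women who are eligible will be randomly allocated to one of the eight intervention arms". The overall design section has baseline assessment "immediately followed by randomization into one of the eight, pre-stratified intervention groups". The abstract lists eight arms and names only site as a stratum.

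**Pooling.** The data analysis section says: "Interactions between interventions will be assessed, and when not present, groups will be combined". The sample size section counts on this: "Lesser numbers are required when using the factorial design, combining cells for comparisons". The multilevel model is justified by provider and centre. Covariates enter if they change the coefficient by 10% or more. The 2x2 trial is not mentioned there.

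**The concern.** A stratification factor is fixed before the draw. If the 2x2 trial is such a factor, a woman is randomised among the four arms of her own 2x2, and the two sets of four arms were not randomised against each other. The baseline calcium tests point the same way. They come before randomisation and are done only in the vitamin D part, so staff must already know which women belong to it.

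The two sets may then differ in their extra exclusions, in the undescribed route of entry, and in taking tablets: the control group section says controls get neither vitamin D nor placebo. The only stated condition for combining groups is that interventions do not interact. That test says nothing about a difference in level between the two sets. A pooled contrast that draws unequally on the two trials would carry part of that difference into the estimated effect.

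**Working it through.** **Inputs.** 110 women per arm and 880 in total (abstract). 20% dropout; fasting glucose difference 0.30 mmol/l, SD 0.5; weight gain difference 4 kg, SD 6.5; HOMA-IR difference 0.44, SD 0.8 (sample size section). The total reproduces: 8 × 110 = 10 × 88 = 880. The point uses these differences and SDs; it does not depend on the stated per-arm numbers.

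I take the "vitamin D arm" of the eligibility text to mean the four arms of the vitamin D/placebo 2x2. Let Δ be the mean outcome in that 2x2 minus the mean in the lifestyle 2x2, apart from intervention effects.

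**Step 1: simple pooled contrasts.** Bias = (share from the vitamin D 2x2 on one side − share on the other) × Δ.

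| Contrast | Shares | Bias |
|---|---|---|
| HE alone (or PA alone) v control + placebo alone | 0/110 v 110/220 | −0.50Δ |
| Any lifestyle v none | 220/550 = 40% v 220/330 = 67% | −0.27Δ |
| Vitamin D alone v placebo alone + control | 110/110 v 110/220 | +0.50Δ |
| Vitamin D v all without it | 220/220 v 220/660 = 33% | +0.67Δ |
| HE+PA (three arms) v no lifestyle (three arms) | 220/330 v 220/330 | 0 |
| Vitamin D v placebo inside its 2x2 | 220/220 v 220/220 | 0 |
| HE margin inside the lifestyle 2x2 | 0/220 v 0/220 | 0 |

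**Step 2: one additive model over all eight arms** (HE, PA, HE+PA, vitamin D; no trial term). The no-lifestyle, no-vitamin D reference is control and placebo alone, half of it from each trial, so the intercept absorbs 0.5Δ. HE alone and PA alone lie wholly in the lifestyle 2x2: 0 − 0.5Δ = −0.5Δ. Vitamin D lies wholly in the other: Δ − 0.5Δ = +0.5Δ. HE+PA has the same mix as its reference: 0.

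**Step 3: size.** The documents give no Δ, so I assume 0.1 to 0.3 SD. For fasting glucose that is 0.1 × 0.5 = 0.05 to 0.3 × 0.5 = 0.15 mmol/l. A bias of 0.5Δ is then 0.025 to 0.075 mmol/l, or 8% to 25% of the 0.30 target; 0.67Δ is 0.033 to 0.10.

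Type I error for HE alone v control + placebo alone, with 110 × 0.8 = 88 completers per arm: SE = √(1/88 + 1/176) = 0.1305 SD. At Δ = 0.3 SD the shift is 0.15/0.1305 = 1.15 standard errors, so a nominal 5% test rejects a true null 21.0% of the time. At Δ = 0.1 SD it rejects 6.7%.

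**Step 4: precision cost of a trial term** (88 per arm, SD units).
- Vitamin D without the term: 88 v 176 in each of two lifestyle levels, averaged. SE = √[(1/88 + 1/176)/2] = 0.0923. With it: 176 v 176. SE = √(2/176) = 0.1066. Ratio 1.15.
- HE or PA without the term: √[(1 + 5/12)/88] = 0.1269. With it: √[(1 + 2/3)/88] = 0.1376. Ratio 1.08. The fractions are the variances of the fitted reference mean, in units of 1/88.
- HE+PA: √(2/264) = 0.0870 either way.

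The lowest power with the term is for HE or PA on HOMA-IR: 0.44/0.8 = 0.55 SD; 0.55/0.1376 − 1.96 = 2.04; power 0.979.

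**The case against.** The strongest reply is that the data analysis section is a short summary in an article. Stratum terms and exact contrasts commonly go in an analysis plan, which is not shown. Silence about a model term would indeed be no finding alone. What stands is narrower: the article itself fixes a pooling rule with a single condition, and names the clustering it will model without its own second stratification factor.

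A reader might infer that the planned analyses are biased. The documents do not support that. They plan none of the unbalanced contrasts above. Each 2x2 is a complete factorial, so combining groups can be read as taking margins inside it, where nothing mixes. The most natural cross-trial pool, HE+PA v no lifestyle, is balanced.

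A reader might also infer, as settled fact, that women were never randomised across all eight arms. The text conflicts on this. The eight-arm reading does not remove the problem, though: exclusions applied to only four of the eight arms would themselves make the sets non-comparable.

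Nor can it be inferred that calcium eligibility is checked too late. It belongs to the baseline measurement, which precedes randomisation.

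Finally, the 10% confounder rule might bring in a trial term. Over the assumed range the bias is 8% to 25% of the glucose target, so it would do so only sometimes, and only if trial is a candidate variable.

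**Conclusion.** The point holds as a conditional one. The article implies that 2x2 membership precedes allocation, contradicts this elsewhere, and has a pooling rule that does not keep comparisons inside a 2x2 or adjust for it. If cells are pooled across trials without a trial term, the bias is −0.5Δ for HE alone and PA alone, +0.5Δ for vitamin D (0.67Δ against all women without it) and −0.27Δ for any lifestyle v none. Within-2x2 margins and the balanced HE+PA pool are safe.

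The size rests wholly on Δ, which is assumed. The documents give no calcium-exclusion rate, no link from those exclusions to the outcomes, and one inclusion period for everyone, so Δ may be small. The route into each 2x2, which is not described, could matter more than the calcium criteria. Against a 0.30 mmol/l target the assumed bias of 0.025 to 0.075 is modest, but it can raise the false-positive rate well above 5%.

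**What to change.** 1. In the abstract, overall design, sample size and randomisation sections, state in the same terms that women are randomised within one of two parallel 2x2 trials, and how a woman enters each. If that is not how allocation works, reconcile those sections with the separate eligibility and baseline testing of the vitamin D part.
2. In the data analysis section, include 2x2 trial, with centre, as a fixed stratum in every model that pools cells. Alternatively, form each contrast inside a 2x2 and then combine the contrasts.
3. State that vitamin D is compared only with placebo inside its own 2x2.

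The cost is wording and one model term, with no new data. Against an unadjusted pooled model, the standard error rises about 8% for HE or PA and 15% for vitamin D, and not at all for HE+PA. That loss is small but not nil; power at the stated effects stays at or above 0.979.

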#### Sample size and power calculation

The primary outcomes of the study are gestational weight gain, fasting glucose and insulin sensitivity in late pregnancy. The numbers needed in each arm (80% power, 5% significance, two tailed alpha) were calculated assuming a 20% drop out. To detect a weight gain difference of 4 kg (mean of 11 kg and standard deviation (SD) of 6.5 kg) we would need 80 women in each arm. To measure a fasting glucose difference of 0.3 mmol/l (mean of 5.0 mmol/l and a SD of 0.5 mmol/l) we would need 85 women in each arm. To find a difference 0.44 for the HOMA-IR (mean of 2.2 and a SD of 0.8) we would need 101 women in each arm. Lesser numbers are required when using the factorial design, combining cells for comparisons. The trial will be conducted in nine European countries (ten study centres) and in each centre 88 women will be recruited (total n = 880) before 20 weeks of pregnancy and randomly assigned to one of the eight arms pre-stratified for centre and 2x2 trial (lifestyle 2x2 or vitamin D/placebo 2x2).

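### The per-arm numbers 80, 85 and 101 do not follow from the stated 80% power, two-sided 5% significance and 20% drop-out, which give about 52, 55 and 65

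*Protocol article*

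**What the plan says.** The section Sample size and power calculation in the protocol article sets one frame for three calculations: "The numbers needed in each arm (80% power, 5% significance, two tailed alpha) were calculated assuming a 20% drop out". The three results follow.

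- Weight gain, difference 4 kg: "mean of 11 kg and standard deviation (SD) of 6.5 kg) we would need 80 women in each arm".
- Fasting glucose, difference 0.3 mmol/l: "mean of 5.0 mmol/l and a SD of 0.5 mmol/l) we would need 85 women in each arm".
- HOMA-IR: "To find a difference 0.44 for the HOMA-IR (mean of 2.2 and a SD of 0.8) we would need 101 women in each arm".

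The section adds that fewer women would be needed if cells were combined under the factorial design, so the three numbers are for unpooled arm-against-arm comparisons. It mentions no correction for multiple comparisons and no allowance for clustering. The abstract gives 110 women per arm and 880 in total.

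**The concern.** Every input to a standard two-sample calculation is printed in this one paragraph, so the results should be reproducible from it. They are not: each stated number is more than one and a half times what the inputs give. The excess is nearly the same for all three outcomes, which points to something common to all of them (significance level, power or an extra allowance) and not to a slip in one SD or difference.

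At stake is the declared error level. If the trial was sized for a stricter level than 5%, the text misreports it, and a reader cannot tell whether a pairwise primary comparison with p = 0.03 was meant to count as positive. If it was not, the stated power or the stated numbers are wrong.

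**Working it through.** **Inputs**, all from Sample size and power calculation: two-sided α = 0.05; power 80%; drop-out 20%, already included in the stated numbers; (difference d, SD) = (4, 6.5), (0.3, 0.5) and (0.44, 0.8). Allocation is equal, with 110 per arm (abstract).

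**Formula.** Completers per arm n = 2(z₁₋α/₂ + z_power)²(SD/d)²; recruited per arm = n/0.8.

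**At the stated 5%.** (1.960 + 0.842)² = 7.849.

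| Outcome | (SD/d)² | n | n/0.8 | Rounded up | Stated | Stated ÷ (n/0.8) |
|---|---|---|---|---|---|---|
| Weight gain | 2.641 | 41.45 | 51.81 | 52 | 80 | 1.54 |
| Fasting glucose | 2.778 | 43.60 | 54.51 | 55 | 85 | 1.56 |
| HOMA-IR | 3.306 | 51.89 | 64.87 | 65 | 101 | 1.56 |

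The plan's figures are not reproduced. Rounding up both before and after inflation gives 53/55/65, and the exact t-test gives at most 54/57/67. One-sided 5% gives 33/35/41 before drop-out, and pooling two cells per side gives 26/28/33 per cell; both move further away.

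**Power of a 5% test.** With m completers per arm, power = Φ(d/SD·√(m/2) − 1.960).

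- At the stated numbers, m = 0.8 × 80 = 64, 0.8 × 85 = 68 and 0.8 × 101 = 80.8:
  - weight gain: Φ(3.481 − 1.960) = 93.6%
  - glucose: Φ(3.499 − 1.960) = 93.8%
  - HOMA-IR: Φ(3.496 − 1.960) = 93.8%
- At 110 per arm, m = 0.8 × 110 = 88: Φ(2.122) = 98%, Φ(2.020) = 98% and Φ(1.688) = 95%.

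**What would give the stated numbers?** With α = 0.05/6 = 0.00833, z₁₋α/₂ = 2.638 and (2.638 + 0.842)² = 12.110. Then n = 63.95, 67.28 and 80.06, and n/0.8 = 79.94, 84.09 and 100.08. One final round-up gives 80, 85 and 101, an exact match. By the same route only α between about 0.00831 and 0.00836 matches. Six is the number of pairs among the four arms of one 2x2 (4 × 3/2).

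**How unique is that?** Each n is the same constant times (SD/d)², so one free constant fits all three.

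- 12.110/7.849 = 1.543. Any multiplier of about 1.542 to 1.5435 on the 5% results, rounded up once, gives 80/85/101.
- α of about 0.0119 with 85% power and n × 1.2 gives 79.94, 84.09 and 100.07, so again 80/85/101.
- With 0.05/6, rounding up at both steps gives 81/0.8 = 101.25, hence 102 for HOMA-IR. The exact match needs a single rounding at the end.

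**Power at 0.0083 with 88 completers.** Φ(4.082 − 2.638) = 93%, Φ(3.980 − 2.638) = 91% and Φ(3.648 − 2.638) = 84%.

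**The case against.** The strongest reply is that the error is conservative. The trial is larger than the stated inputs require, 110 per arm gives 95% to 98% pairwise power at 5%, and no recruitment target changes. That stands, and it limits the point to a wrong statement of level, power or number; it does not make the paragraph correct.

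A second reply is that nothing in the article mentions six comparisons or a Bonferroni correction. That also stands. A reader might take the exact match at 0.05/6 as proof of one, but the three agreements are not independent confirmations. An unstated clustering allowance of about 1.54 would do equally well; the Data analysis section plans multilevel models for clustering, though no such allowance is stated either.

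Three further readings are tempting and are not supported.

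- *The analysis drops the correction.* The Data analysis section names only p < 0.10, for effect modification, but a per-comparison threshold is commonly left to a statistical analysis plan, which is not shown.
- *Testing at 5% gives a family-wise error of about 20% per outcome.* That supposes all six unpooled pairwise tests in a 2x2. The article does not specify that family, and says groups will be combined when interventions do not interact.
- *The hidden correction paid for half the sample.* The excess is (80 − 52)/80 = 35%, (85 − 55)/85 = 35% and (101 − 65)/101 = 36% of the stated numbers, about a third.

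**Conclusion.** The point holds as an internal inconsistency in the sample size section. At the stated level, power and drop-out, the numbers should be about 52/55/65, not 80/85/101. Equivalently, the stated numbers give a 5% pairwise test about 94% power where the text says 80%. This rests only on printed inputs and the usual comparison of two means with equal arms; the choice between normal and t formulas, and of rounding, shifts the result by two or three women per arm at most.

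That the numbers were computed at 0.05/6 is the neatest explanation and a strong inference, not a documented fact. The finding does not depend on it. The trial is not underpowered at either level.

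**What to change.** The sponsor should check its own calculation and restate the sample size paragraph according to what it finds.

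1. **If 0.05/6 was used:** replace the 5% level by a two-sided 0.0083 per pairwise comparison (0.05/6), and judge the unpooled primary pairwise arm comparisons at that level. Say that it does not cover the three primary outcomes jointly. Power with 88 completers per arm is then about 93%, 91% and 84%.
2. **If another allowance was used**, such as one for clustering: state it and its size.
3. **If none was used:** correct the numbers to 52, 55 and 65, or keep them and restate the power as about 94%.

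The level of 0.0083 should be written in only once the sponsor confirms it. If the cause was something else, that edit would add a false statement and could impose a pairwise threshold on comparisons that pool cells.

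The cost is a few sentences. The total of 880 stays as it is in every case. The only downside, in the first case, is a less favourable stated significance level.
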